### Settings/participants

Participation calls were sent out by e-mail to the 4 major umbrella organizations for nursing homes. To maximize sample size, each of the 755 Flemish nursing homes was also individually contacted by means of a flyer. Enrollment was voluntarily, albeit 5 inclusion criteria needed to be met. These were: (1) The ward unit must be focused on persons with dementia, or at least have a mixed population. (2) A minimum of 4 to a maximum of 6 ward staff members can participate. (3) At least one of these members must stem from either middle or executive management. This person must be directly involved with the participating ward (e.g. work there or coordinate tasks) and delegate all information and assessment requirements to the other members. These other participants can be either care or non-care professionals as long as they interact with the residents and their families on a regular basis. (4) Enlisting wards enroll in both the training as well as the research module. (5) The nursing home has not participated in ‘We DECide’, and will not participate in other ACP research for the duration of the training.

One hundred ninety nursing homes responded to the flyer, whereupon they received more information. Forty-eight of these 190 nursing homes subscribed for a total of 65 wards (311 participants). The primary reasons for not participating in the study were resistance from management or staff members, reluctance to send in audio files (see also: OPTION) and the long-term duration of the intervention. We also received a lot of interest from psychiatric wards, which we unfortunately had to decline because the intervention was not tailored to the specific population.

BG distributed the 65 nursing home wards in the intervention and control group through simple randomization in Excel before any measurements were conducted. The randomization was conducted at the nursing home level (48) at a 1:1 ratio to avoid contamination between clusters in a single nursing home. This resulted in 34 wards in the intervention group and 31 wards in the control group. Clusters, participants and trainers were blinded of group assignment (single-blind trial). Participants completed written informed consent forms upon enrollment before the randomization.

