The homework assignments will be discussed during the first hour of the second workshop. Participants will reflect on their conversations and offer each other suggestions on how to improve their communication skills. This information will be noted by BG as part of his task to oversee the research component of the intervention. Another role play exercise will be introduced during the second hour. It will focus on ACP conversations in crisis situations. If participants have not re-enacted a case during workshop 1, they will be invited to take up a role. At the end, there will be a discussion about lessons learned. Both segments are to be assisted by the trainer. After a short break, participants will be invited to sit down with their other staff members to discuss their ACP policy. They will be asked to list a number of opportunities and ways to improve their policy in a period of 3 to 9 months. Recommendations to achieve person-centered care will be given on a single page document to assist them in this task. This document is based on the ACP Guidelines which were previously used in ‘We DECide’, but were found to be too cumbersome and time-consuming [20]. After 1 hour, both wards will come together again to discuss their opportunities for improvement. The trainer and other ward members will give recommendations for improving the achievability of these ideas. The wards will be contacted in 3 and in 9 months to check progress on their objectives and to provide further incentives for improving their policy. This discussion will last 30 min. During the last half hour, participants will fill in the IFC-SDM questionnaire, which assesses the competence, importance and frequency at which staff members engage in SDM (see also: IFC-SDM). They will also fill in an evaluation form concerning their experiences during both workshops and the homework assignment. Details on post-training measurements and follow-up interviews will be discussed.

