### Study design

The study uses a cluster randomized controlled design, with clusters at the ward level. ‘We DECide optimized’ will be implemented in the intervention group, while the control group receives no training. After all measurements have been simultaneously conducted in both groups, excluding the interviews regarding long-term implementation results, the control group will receive training as well. Data will be collected through a pretest-posttest model, with measurements at 5 time points. These are (T0) 3 months prior to training, (T1) directly after the last training session, (T2) 3 months after training, (T3) 6 months after training and (T4) 9 months after training (Fig. 3. Study overview).

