### Outcome measurements

#### Primary outcomes

Our primary outcome is the use of SDM in formal ACP conversations. This outcome is measured at both the participant and the resident level through 3 instruments, which are selected based on their usage in comparable (inter)national research and with regard to their psychometric properties. Both observational and self-descriptive instruments are used, since the triangulation of data is considered especially important to report on effective change management in an adequate manner. For measurements on the resident level, brief and easily accessible questionnaires are chosen so as not to overburden the person with dementia or his or her family. See also: Fig. 3. Study overview*.*OPTION-12 is a valid and reliable observational instrument which measures the involvement of patients by clinicians during consultations (α = 0.79) [28, 29]. Observers score 12 items on SDM on a five-point Likert scale ranging from ‘the behavior is not observed’ to ‘the behavior is exhibited to a very high standard’. In this study, we use the Dutch translation to assess the extent to which nursing home staff involve residents and their families during formal ACP discussions. Participating wards send in 2 audio files of formal ACP conversations at the pretest stage as well as 3 and 6 months after training. These audio files are recorded by the same participants at the different time points. Recordings are rated by two blind researchers. Both read through the OPTION training manual beforehand. During the course of the feasibility study, OPTION-5 was developed [30, 31]. Though the latter differentiates better between various levels of patient involvement, both show good interagreement and correlate well with each other [32]. For this reason and so as not to differentiate from the feasibility study, we continue to use OPTION-12 during the course of this study.The ‘Shared Decision Making Questionnaire’ (SDM-Q) is an internationally validated questionnaire which assesses the implementation of SDM in clinical conversations. It can be used to investigate the effectiveness of interventions which aim to increase said level of SDM [33]. It consists of 9 items which are rated on a six-point Likert scale ranging from ‘completely disagree’ to ‘completely agree’. It is filled in separately by both the healthcare professional (SDM-Q-DOC) and the patient (SDM-Q-9) to assess their view on the conversation. The instrument was translated and validated in Dutch (SDM-Q-DOC α = 0.87, SDM-Q-9 α = 0.88) [34]. For this study, the SDM-Q was used in conjunction with the OPTION audio files to compare data from both instruments. Residents and their families received a pre-stamped envelope which they can use to send the SDM-Q-9 to us without any involvement from the nursing home ward.The Dutch variant of collaboRATE is used to assess further the view of residents on their involvement in ACP conversations. [35] This questionnaire gauges the level of SDM in 3 items on a 10-point Likert-scale, ranging from ‘no effort was made’ to ‘every effort was made’. Both are discriminative as concurrent validity to other instruments, including the SDM-Q, is established [36]. For this study, collaboRATE is filled in at the same time as the SDM-Q and sent in the same pre-stamped envelope. Due to the limited amount of items, it should also be more accessible in situations where residents and families consider the SDM-Q to be too burdensome.

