
#### Secondary outcomes

Our secondary outcomes provide more insight into the mechanisms which might facilitate the use of SDM in ACP conversations. These include the view of participants on their competence, a measurement of the actual ACP policy at the ward level, and support from management. All secondary outcomes are measured by means of self-report questionnaires.The IFC-SDM measures nine behavioral aspects needed to engage in SDM and is based on the three-step talk model [16]. Each aspect is measured on three scales: how important participants find this behavior; how frequently they put this behavior into practice; and how competent they feel in doing so. To distinguish between the use of SDM in different work settings, the questionnaire assesses these behaviors in three circumstances: for conversations at the time of admission, during daily practice and in crisis situations. Items are scored on a 5-point Likert scale, ranging from ‘not important at all’ to ‘extremely important’. Participants can also indicate that they do not know. The IFC-SDM is based on earlier work by our research group and was pilot tested before the feasibility study [20]. No changes were made afterwards. The questionnaire is completed in the pretest stage, immediately after the last training session and after 3 and 6 months.The ‘Advance Care Planning Questionnaire’ (ACPQ) measures the organization of ACP at the ward level. 45 questions assess how and with whom ACP is discussed at the time of admission, in a crisis situation and at the start of palliative care. Answers are then compared with practice guidelines for communication on end-of-life issues for persons with dementia in nursing homes and scored either 0 or 1 for a total of 45 points. The higher the score, the more the guideline criteria are met. The ACPQ was piloted during the feasibility study in the form of a group audit [20]. This method was found to be too time-consuming considering the current sample size. It also did not allow for differentiating scores between care professionals and management staff. For this reason, the audit was turned into a questionnaire. One item was rewritten to reflect the underlying question better. The ACP is filled in by all participants at the pretest stage and after 3 and 6 months.The self-constructed ‘Supporting Advance Care Planning’ (SACP) assesses the support from management in discussing ACP and optimizing its organization (see Additional files 1 & 2). Participants answer eight items on two scales: how important they find the item and how much it is implemented at the ward level. These eight questions are based on the barriers which were most frequently mentioned at the end of the feasibility study. The items are scored on a 5-point Likert scale, ranging from ‘not important at all’ to ‘extremely important’. The questionnaire is filled in the pretest stage and after 3 and 6 months.

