## Discussion

This article deals with the design of a cluster-randomized controlled trial which measures the effectiveness of ‘We DECide optimized’, a communication training program for nursing home staff, on the use of SDM in formal ACP conversations. Due to the complex nature of dementia, it is crucial for residents and their families to be able to express their preferences and wishes in an informed and timely manner. Furthermore, both clinicians and residents hesitate to initiate conversations due to a lack of information and experience. ‘We DECide optimized’ addresses both concerns by training nursing home staff in the use of SDM: participants receive information on SDM and ACP and engage in various role-play exercises with help from an experienced trainer. One strength of this training is the inclusion of professionals from all backgrounds to engage the ward as a whole in discussing ACP. Furthermore, each ward delegates one member of management to stimulate the implementation of the training at the ward level. An additional strength of the training is our multi-level approach: by engaging the clinical, organizational and resident level, all stakeholders in ACP are invited to immerse themselves in conversation and further encourage person-centered care. The triangulation of data and the inclusion of both quantitative and qualitative data allows for extensive reports on the effectiveness of the training. It also allows us to report on facilitators and barriers for future interventions which seek to enhance the use of SDM in ACP conversations. One limitation is that enrollment in the training is voluntary: wards which are not motivated are not likely to participate. Since this is a single-blind trial (due to the control group receiving the training only at a later date) there should be no intentional bias on the part of the participants. Another limitation concerns the upper limit of 6 participants for each ward. Ideally, every staff member who engages in daily conversation with residents and their families should receive the training, thus truly achieving a ward-level approach to ACP. Since two wards receive training together, we set a maximum of 12 participants per group so as not to hinder interaction and assimilation. Participants are also stimulated to disseminate the training components and materials to other staff members and/or incorporate elements thereof into their own practice policy.

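### Staff and trainers are described as blinded, but a training versus no-training design unblinds them from the first workshop, leaving staff-rated outcomes open to reporting bias

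*Protocol article*

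**What the plan says.** Settings/participants, at the end of the randomization paragraph: "Clusters, participants and trainers were blinded of group assignment (single-blind trial". The Discussion gives the mechanism, "due to the control group receiving the training only at a later date", and draws the conclusion that "there should be no intentional bias on the part of the participants".

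Under Study design, the intervention group receives the programme "while the control group receives no training". The timing follows: "After all measurements have been simultaneously conducted in both groups, excluding the interviews regarding long-term implementation results, the control group will receive training as well".

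On measurement, the primary outcome combines OPTION-12, SDM-Q (a professional and a patient version) and collaboRATE. For OPTION-12, "Recordings are rated by two blind researchers". For IFC-SDM, ACPQ and SACP, "All secondary outcomes are measured by means of self-report questionnaires". Under Workshop 2: "During the last half hour, participants will fill in the IFC-SDM questionnaire".

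**The concern.** The article credits the trial with a property that its intervention rules out. A full-day equivalent of role play and teaching, with homework in between, cannot be hidden from those who attend it, nor its absence from those who do not. The trainers deliver it in person.

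The article also uses the blinding statement to set aside participant bias, although the same participants rate themselves on most of the staff-level outcomes. One stated hypothesis is that training raises perceived importance, competence and frequency, which is exactly what self-ratings by people who know they were trained can inflate. A reader who accepts the blinding statement would take a between-arm difference on these scales as a training effect, without allowing for a shift in reporting.

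**Working it through.** No arithmetic decides this point. It rests on comparing the sections of the article.

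**1. What could be masked, and until when.**
- Enrollment and consent precede randomization, and randomization precedes all measurements (Settings/participants). T0 is 3 months before training (Study design). Wards could therefore be unaware of their arm at T0, if they were not told.
- From workshop 1, intervention staff are in the training (Intervention design; Workshop 1). Controls are not trained while the questionnaires and recordings are being collected (Study design).
- T1 is directly after the last session, and T2 and T3 are 3 and 6 months after training. At each of these, every staff respondent knows whether they attended two workshops. Being promised training later hides none of this.
- The trainers know which wards they have taught.

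**2. Who rates each outcome after training.**

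| Score | Role | Rated by | Rater's knowledge after training |
|---|---|---|---|
| OPTION-12 | primary | two researchers, stated blind | blind, extent not specified |
| SDM-Q-DOC | primary | staff | know own exposure |
| SDM-Q-9 | primary | resident or family, returned by post | not stated |
| collaboRATE | primary | resident or family, same envelope | not stated |
| IFC-SDM | secondary | staff | know own exposure |
| ACPQ | secondary | staff | know own exposure |
| SACP | secondary | staff | know own exposure |

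Four of seven scores come from staff who know their exposure: one of four within the primary outcome and three of three secondary outcomes.

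**3. The T1 measurement of IFC-SDM.** The instrument is built on the three-step talk model (Secondary outcomes), which is the model taught in workshop 1. The intervention group completes it in the closing half hour of workshop 2. Controls have no workshop, so their simultaneous T1 form must be completed in some other setting. The arms therefore differ at T1 in setting as well as in training.

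**4. The label.** Clusters, participants and trainers are all called blind, as are the OPTION-12 researchers, yet the trial is called single-blind. Of these groups, only the OPTION-12 researchers can be blind after training has begun.

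**5. What blind scoring does not cover.** Wards record the conversations and send in two audio files per time point (Primary outcomes). Blind scoring protects the rating. It does not protect against aware staff influencing which conversations are held, recorded and sent.

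**6. Size.** Required sample size gives power, cluster size, intraclass correlation and 32 wards per condition, but no effect size or standard deviation. A reporting shift cannot be expressed as a share of a planned effect.

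**The case against.** The strongest defence is a narrower reading. The blinding sentence closes the randomization paragraph, all wards enrolled for training, and the Discussion ties blinding to the delayed start. The authors may mean only that wards were not told their arm label. That is plausible up to the start of training, but it does not help at T1 to T3, and the Discussion applies the claim to participants without a time limit.

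Several stronger readings are tempting, and the documents do not support them:
- A reader might infer that the plan declares participants free of all bias. It says only that intentional bias should be absent. The inference still fails, because knowing one has been trained can shift self-ratings with or without intent.
- A reader might count SDM-Q-9 and collaboRATE with the staff ratings, since intervention wards receive campaign posters, cards and pages. Those forms are returned by residents or families without ward involvement, nothing says respondents are told the allocation, and the campaign is itself part of the intervention. Its influence cannot simply be called bias.
- A reader might back-calculate a detectable difference from 32 wards of 5 staff and set a bias against it. That would be an inferred figure, and it rests on five staff per ward, whereas OPTION-12 has two recordings per ward per time point.
- A reader might see reporting bias in the feasibility result of improved competence without improved observed use (Background). Skill that precedes a change in practice would give the same pattern.
- A reader might conclude that OPTION-12 must carry the confirmatory claim alone. The article gives a reason for triangulating, and OPTION-12 depends on recordings supplied by aware wards. That choice is a debatable trade-off, not a correction.

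**Conclusion.** The point holds as a statement that is wrong as written. After the first workshop, wards, staff participants and trainers are not blind, and the inference about participant bias has no basis in the design. The consequence is confined mainly to the four staff-rated scores and is clearest for IFC-SDM at T1. OPTION-12 scoring keeps its protection to the extent that its raters are in fact blind. SDM-Q-9 and collaboRATE are affected less directly, if at all.

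The direction of concern is towards favouring the intervention, on the assumption that trained staff tend to rate themselves more highly. The size is unknown. Allocation, data collection and the mixed model are unaffected. What changes is what the trial may conclude from the staff self-reports.

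**What to change.** 1. In Settings/participants, replace the blinding sentence: wards, staff participants and trainers are unblinded from the first workshop, and only OPTION-12 scoring is blind. The sponsor should confirm what the raters are blind to (arm, time point or both), since the text does not say. If wards were unaware of allocation up to T0, that can be stated separately.
2. In the Discussion, delete the inference about intentional bias. List reporting bias in staff-rated outcomes as a limitation, and note that wards aware of their arm also choose and send the recordings.
3. State that results on SDM-Q-DOC, IFC-SDM, ACPQ and SACP will be interpreted as unblinded, supportive evidence beside the blind-rated OPTION-12.
4. Rest the IFC-SDM comparison between arms on the 3- and 6-month measurements, and report T1 descriptively.

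The cost is wording and a rule of interpretation. IFC-SDM is already collected at 3 and 6 months, so no new measurement or procedure is needed. The one loss is that the immediate post-training IFC-SDM comparison no longer serves as a test between arms.

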### Outcome measurements

#### Primary outcomes

Our primary outcome is the use of SDM in formal ACP conversations. This outcome is measured at both the participant and the resident level through 3 instruments, which are selected based on their usage in comparable (inter)national research and with regard to their psychometric properties. Both observational and self-descriptive instruments are used, since the triangulation of data is considered especially important to report on effective change management in an adequate manner. For measurements on the resident level, brief and easily accessible questionnaires are chosen so as not to overburden the person with dementia or his or her family. See also: Fig. 3. Study overview*.*OPTION-12 is a valid and reliable observational instrument which measures the involvement of patients by clinicians during consultations (α = 0.79) [28, 29]. Observers score 12 items on SDM on a five-point Likert scale ranging from ‘the behavior is not observed’ to ‘the behavior is exhibited to a very high standard’. In this study, we use the Dutch translation to assess the extent to which nursing home staff involve residents and their families during formal ACP discussions. Participating wards send in 2 audio files of formal ACP conversations at the pretest stage as well as 3 and 6 months after training. These audio files are recorded by the same participants at the different time points. Recordings are rated by two blind researchers. Both read through the OPTION training manual beforehand. During the course of the feasibility study, OPTION-5 was developed [30, 31]. Though the latter differentiates better between various levels of patient involvement, both show good interagreement and correlate well with each other [32]. For this reason and so as not to differentiate from the feasibility study, we continue to use OPTION-12 during the course of this study.The ‘Shared Decision Making Questionnaire’ (SDM-Q) is an internationally validated questionnaire which assesses the implementation of SDM in clinical conversations. It can be used to investigate the effectiveness of interventions which aim to increase said level of SDM [33]. It consists of 9 items which are rated on a six-point Likert scale ranging from ‘completely disagree’ to ‘completely agree’. It is filled in separately by both the healthcare professional (SDM-Q-DOC) and the patient (SDM-Q-9) to assess their view on the conversation. The instrument was translated and validated in Dutch (SDM-Q-DOC α = 0.87, SDM-Q-9 α = 0.88) [34]. For this study, the SDM-Q was used in conjunction with the OPTION audio files to compare data from both instruments. Residents and their families received a pre-stamped envelope which they can use to send the SDM-Q-9 to us without any involvement from the nursing home ward.The Dutch variant of collaboRATE is used to assess further the view of residents on their involvement in ACP conversations. [35] This questionnaire gauges the level of SDM in 3 items on a 10-point Likert-scale, ranging from ‘no effort was made’ to ‘every effort was made’. Both are discriminative as concurrent validity to other instruments, including the SDM-Q, is established [36]. For this study, collaboRATE is filled in at the same time as the SDM-Q and sent in the same pre-stamped envelope. Due to the limited amount of items, it should also be more accessible in situations where residents and families consider the SDM-Q to be too burdensome.
